#### Analysis

Table 2 outlines the planned psychometric analyses to be conducted as part of the ISBUS project. Analyses will be adapted to the actual sample size achieved (ie, ≥50 or ≥100) and will include, at the very least, exploratory factor analysis to assess structural validity; correlations and group comparisons for construct validity; and Cronbach α for internal consistency. Given the small sample size expected and the likely skewed distribution, it is anticipated that nonparametric statistics will be used (eg, Spearman ρ correlations and unweighted least squares estimation) [20,57].

**Table 2 table2:** Planned psychometric analyses for the ISBUS^a^.

Stage and measurement property		Analysis	Evaluative criteria
Stage 3: final item selection			
	Structural validity		
		If n≥50 but <100: exploratory factor analysis using unweighted least squares for small samples	Loadings ≥0.40 Communalities ≥0.30 Chi-square test *P*>.5 RMSEA^b^<0.08 TLI^c^≥0.90 RMSR^d^≤0.08
		If n≥100: CFA^e^ or EFA^f^; Rasch modelling	CFA: same criteria as EFA Rasch: fit residuals between −2.5 and 2.5 Ordered thresholds
	Hypothesis testing for construct validity		
		Correlate ISBUS burden score with iMCD^g^ quality of life VAS^h^, PHQ-15^i^ score, and EQ-5D-5L utility	At least moderate correlations (rs≥0.30)
		Compare participants with symptoms impacting daily activities vs those without such impact	At least a moderate difference (d≥.05)
	Internal consistency		
		Cronbach α	Cronbach α≥0.70
Stage 4: preliminary measures of change			
	Test-retest reliability		
		ICC^j^ in participants reporting no change in health status	ICC≥0.70
	Measurement error		
		Standard error of measurement and MDC95^k^ in participants reporting no change in health status	MDC95<MIC^l^
	Responsiveness		
		SRM^m^ for improved, stable, and worsened group	SRM≥0.2 (improved and worsened group) and <0.2 (stable group)
		ROC AUC^n^ for improved subgroup	ROC AUC≥0.70 (improved group)
	Meaningful change (MIC)		
		Anchor-based MIC (mean and median improvement) for the minimally improved group	Correlation between anchor and change ≥0.30
		Distributional analyses (0.5 × SD, standard error of measurement) in the improved health group	MIC>MDC95
		Responder difference (mean and/or binary method)	More responders in the improved group than in the nonimproved group

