### Stage 4: Preliminary Measures of Change

#### Overview

In order to provide initial insights into meaningful change scores on the new symptom burden scale, a mixed methods approach will be used. First, the draft PROM will be readministered to all participants from stage 3, alongside a global measure of perceived change in health status, after 2 months (informed by expert clinical opinion). This will allow estimates of stability (test-retest reliability and measurement error) in those without change, and estimates of change (responsiveness, minimal important change [MIC], otherwise known as meaningful score difference [58]) in those with change. Second, as iMCD is a rare disease, it is possible that insufficient participants are recruited at follow-up and/or insufficient change is observed to reliably estimate the MIC. Accordingly, in addition to quantitative estimates, semistructured qualitative debriefing interviews will be carried out with patients who have completed the survey at both time points to understand what constitutes a meaningful improvement from the patients’ perspective [19,20]. By triangulating this information with expert advisory input, the aim is to provide preliminary evidence on meaningful change using a natural history (ie, noninterventional) approach.

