#### Participants and Recruitment

In stage 4, as many participants as possible who completed the stage 3 survey will be recruited to complete the survey a second time (by direct email invitation). A minimum target sample of at least 20 responses is established to help estimate test-retest reliability. However, the actual number of participants recruited may vary, and analyses will be adapted and interpreted with this in mind. Supplementary cognitive interviews to help support meaningful change estimates will be carried out with 10 people living with iMCD. These participants will be purposively sampled from those completing the stage 4 survey, aiming to ensure sufficient breadth in symptom burden (stage 4), perceived change in health (stage 3 to stage 4), and gender [20].

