#### Analysis

As this study uses a natural history framework for exploring change (ie, it is noninterventional), all change statistics should be considered informative but preliminary only. Reliability and measurement error statistics can be calculated in the subsample of participants whose health status “stayed the same” between stage 3 and stage 4. Specifically, the intraclass correlation coefficient will be used to assess test-retest reliability, while the standard error of measurement and minimum detectable change at the 95% confidence level will be used to estimate measurement error in “stable” participants.

Preliminary analyses of responsiveness (ie, in the absence of an intervention) will be estimated using the standardized response mean (for improved, stable, and worsened participants) and the receiver operating characteristic area under the curve for the improved subgroup.

To estimate improvement-based MIC, the mean and median change in symptom burden (between stage 3 and stage 4) among participants who reported a minimal improvement in health (ie, “improved somewhat”) will form the primary anchor-based MIC. A secondary anchor approach will compare change in symptom burden with change in PHQ-15 scores, with an “improved” group defined by (1) a PHQ-15 score greater than or equal to the estimated MIC for the PHQ-15 of 3 points [61] and/or (2) categorical improvement in PHQ-15 clinical cutoff groups (eg, from “moderate” to “mild” symptoms) [55]. These anchor methods will be supplemented with distribution-based analyses using standard approaches (ie, 0.5 × SD and standard error of measurement) [59]. Change in worsened groups will be calculated and reported for comparative purposes but is not the primary focus of interest. Finally, responder difference will be estimated using (1) the binary method, whereby the proportion of people in improved vs not improved subgroups experiencing improvement above the MIC is estimated; and (2) the mean method, whereby the difference in mean burden change for the improved vs not improved subgroups is calculated [62].

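### Table 2 takes the standard error of measurement from two incompatible groups, and takes 0.5 × SD from the improved subset although all 51 stage 3 completers are available

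*Protocol article*

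**What the plan says.** Table 2 of the protocol article uses the SEM in two rows of its stage 4 part.

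- **Measurement error row:** SEM and MDC95 are computed "in participants reporting no change in health status".
- **Meaningful change, distributional row:** "Distributional analyses (0.5 × SD, standard error of measurement) in the improved health group". The criterion beside it is that the minimum important change (MIC) exceeds MDC95.

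The stage 4 text agrees with the first row. The Overview promises "estimates of stability (test-retest reliability and measurement error) in those without change". The Analysis subsection says "Reliability and measurement error statistics can be calculated in the subsample of participants whose health status" was unchanged between the two surveys, and adds that "the standard error of measurement and minimum detectable change at the 95% confidence level will be used to estimate measurement error" in stable participants.

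The same subsection later supplements the anchor methods with "distribution-based analyses using standard approaches (ie, 0.5 × SD and standard error of measurement") and names no group for them. The improved-group wording therefore appears only in the table.

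On numbers, the stage 4 recruitment section states: "A minimum target sample of at least 20 responses is established to help estimate test-retest reliability". The Results section reports 51 stage 3 completers and 32 follow-up surveys by March 2026. The number who improved is not given.

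**The concern.** The SEM describes scatter around a true score that has not moved. People who say they have improved are those whose true score is least likely to have stayed put. If their two scores are used, differences in how much they improved enter the SEM, and in the agreement form the average improvement enters as well. An analyst who followed Table 2 literally could report two SEMs for one instrument. The one in the distributional row would also differ from the SEM behind the MDC95 named as the criterion in that row.

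The half-SD benchmark raises a different question. It is conventionally a fraction of the between-patient spread in the target population. Taking it from people selected on their outcome uses fewer observations and a narrower group than the study already holds. Few participants may report a small improvement, and the Overview itself warns that too little change may be seen. The distribution-based values could then carry noticeable weight when the advisors agree a recommended threshold.

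**Working it through.** The article gives no SD, SEM, ICC or MIC estimate, so there is no published figure to reproduce. The check has three parts.

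**1. Groups side by side**

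| Place | Statistic | Group |
|---|---|---|
| Table 2, Measurement error | SEM, MDC95 | no change |
| Stage 4 Overview | measurement error | no change |
| Stage 4 Analysis, first paragraph | SEM, MDC95 | no change |
| Stage 4 Analysis, distribution-based methods | 0.5 × SD, SEM | none named |
| Table 2, Meaningful change | 0.5 × SD, SEM | improved |

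The SEM has two conflicting assignments. The 0.5 × SD has only one, so it is not contradicted.

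**2. Size of the SEM discrepancy, if the improved participants' two scores are used**

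Assumptions, none from the article: baseline SD = 1; ICC 0.70 to 0.90; mean true improvement m = 0.3 to 0.8; SD of true change s = 0 to 0.5.

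- Stable group: SEM = SD × √(1 − ICC), which is 0.548 at ICC 0.70, 0.447 at 0.80 and 0.316 at 0.90. MDC95 = 1.96 × √2 × SEM, which is 1.52, 1.24 and 0.88.
- Improved group, consistency form: √((2·SEM² + s²)/2).
- Improved group, agreement form: √((2·SEM² + s² + m²)/2).

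Example with ICC 0.80 (SEM² = 0.20), m = 0.5, s = 0.3:

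- consistency: √((0.40 + 0.09)/2) = √0.245 = 0.495, and 0.495/0.447 = 1.11;
- agreement: √((0.40 + 0.09 + 0.25)/2) = √0.370 = 0.608, and 0.608/0.447 = 1.36.

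Over the whole assumed range the ratio is 1.00 to 1.50 (consistency) and 1.07 to 2.33 (agreement). The value 1.00 arises when everyone improves by the same amount. If the SEM is instead a baseline SD times √(1 − stable-group ICC), none of this inflation occurs.

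**3. Precision of the SD behind 0.5 × SD**

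The 95% CI for an SD, as a multiple of its estimate, runs from √((n−1)/χ²(0.975; n−1)) to √((n−1)/χ²(0.025; n−1)).

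| n | Source | Lower factor | Upper factor |
|---|---|---|---|
| 5 | assumed improved group | √(4/11.143) = 0.60 | √(4/0.484) = 2.87 |
| 10 | assumed improved group | √(9/19.023) = 0.69 | √(9/2.700) = 1.83 |
| 51 | stage 3 completers | √(50/71.420) = 0.84 | √(50/32.357) = 1.24 |

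Halving the SD leaves the factors unchanged. The upper limit is 2.87/0.60 = 4.8 times the lower at n=5, 1.83/0.69 = 2.7 times at n=10, and 1.24/0.84 = 1.5 times at n=51. The intervals assume normal scores. The article expects skew, so they are approximate.

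The 51 can be treated as core participants. Their recruitment ended in November 2025, the Brazilian approval is dated December 11, 2025, and the Results section describes recruitment in Brazil separately, as still ongoing.

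**The case against.** The best defence is that the row is loosely worded and little depends on it. Four stronger readings are tempting, and the article does not support them.

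- **That the SEM is certainly inflated.** The article gives no formula. An analyst could use a baseline SD with the stable-group ICC, and no true change would enter. The inflation is conditional.
- **That this SEM determines the MIC.** The primary MIC is the mean and median change among those who improved somewhat, with a PHQ-15 anchor second. Distribution-based values are supplementary, and the final recommendation also draws on interviews and advisors, with no threshold applied. The only MDC95 in the article comes from stable participants, so the MDC95 side of the criterion keeps its stable-group basis.
- **That 0.5 × SD is contradicted, or mixes change with error.** No other section gives it a group, and a baseline SD contains no change between surveys. The article does not say which SD is meant. The objection here is precision and selection only.
- **That the improved group is known to be tiny.** Its size is not reported. It is a subset of the 32 follow-ups so far; 5 and 10 are assumptions.

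It is also fair to say that the stable group is a subset of unknown size, and that the article calls all change statistics preliminary and says analyses will be adapted to the numbers obtained. This lowers the consequence. It does not reconcile the two SEM assignments, because the article names a group in each place and the groups are incompatible.

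**Conclusion.** The conflict over the SEM is real and stands in the current text: one row of Table 2 names the improved group, while the Measurement error row and the stage 4 text name participants without change. If improved participants' scores are used, the SEM could be up to 1.50 times (consistency) or 2.33 times (agreement) the stable-group value under the assumptions shown, and equal to it in the mildest consistency case. Whether that happens depends on a formula the article does not state.

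The 0.5 × SD point is an improvement available from data already collected, not a contradiction. Using all 51 baseline values narrows the CI factors from 0.69 to 1.83 (assumed n=10) to 0.84 to 1.24.

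The importance is moderate. The line should be corrected before the stage 4 analysis, but the anchor-based MIC does not rest on it.

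**What to change.** In the distributional row of Table 2, replace the improved-group wording with two explicit sources:

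- *0.5 × SD: stage 3 baseline SD of the ISBUS burden score in all core participants (n=51).*
- *SEM: the value from participants whose health stayed the same, identical to the Measurement error row.*

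Add the same groups to the sentence on distribution-based methods in the stage 4 Analysis subsection, and report the number of stable participants beside the SEM so that its precision can be judged.

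The cost is one table line and a matching phrase in the text. No new data are needed, and stage 4 was still ongoing at submission, so the change can be made before its results are reported.

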### Stage 4: Preliminary Measures of Change

#### Overview

In order to provide initial insights into meaningful change scores on the new symptom burden scale, a mixed methods approach will be used. First, the draft PROM will be readministered to all participants from stage 3, alongside a global measure of perceived change in health status, after 2 months (informed by expert clinical opinion). This will allow estimates of stability (test-retest reliability and measurement error) in those without change, and estimates of change (responsiveness, minimal important change [MIC], otherwise known as meaningful score difference [58]) in those with change. Second, as iMCD is a rare disease, it is possible that insufficient participants are recruited at follow-up and/or insufficient change is observed to reliably estimate the MIC. Accordingly, in addition to quantitative estimates, semistructured qualitative debriefing interviews will be carried out with patients who have completed the survey at both time points to understand what constitutes a meaningful improvement from the patients’ perspective [19,20]. By triangulating this information with expert advisory input, the aim is to provide preliminary evidence on meaningful change using a natural history (ie, noninterventional) approach.

#### Participants and Recruitment

In stage 4, as many participants as possible who completed the stage 3 survey will be recruited to complete the survey a second time (by direct email invitation). A minimum target sample of at least 20 responses is established to help estimate test-retest reliability. However, the actual number of participants recruited may vary, and analyses will be adapted and interpreted with this in mind. Supplementary cognitive interviews to help support meaningful change estimates will be carried out with 10 people living with iMCD. These participants will be purposively sampled from those completing the stage 4 survey, aiming to ensure sufficient breadth in symptom burden (stage 4), perceived change in health (stage 3 to stage 4), and gender [20].

#### Data Collection

All stage 3 participants will receive an invitation with a link to the stage 4 online survey by email 2 months after they initially completed the survey. The stage 4 survey is a reduced form of the stage 3 survey, omitting most of the background questions (only questions on treatment remain) and the questions on the importance of symptoms. In addition, in order to measure and benchmark clinical change (or lack thereof) in participants’ perceived health, a self-report global impression of change will be used as the primary anchor [59]. The health transition item from the Short Form 36 Health Survey (ie, compared to when you last completed this questionnaire, would you say your overall health has improved a lot, improved somewhat, stayed the same, worsened somewhat, or worsened a lot) will be adapted to estimate changes in health status [60]. Global anchors capture the multidimensional experience of health and are widely used and understood. However, as a secondary construct-specific anchor, existing estimates of MIC for PHQ-15 and/or preestablished clinical cutoffs for the measure will be used [55,61].

Using a semistructured topic guide (Multimedia Appendix 3), the supplementary cognitive interviews are intended to identify meaningful changes from the patients’ perspective. Specifically, after consent procedures, participants will complete the shortened (finalized) version of the novel PROM to refamiliarize themselves with the instrument. They will then be shown their symptom profile (and overall burden score) from the stage 4 survey on screen. Participants will then be asked questions to identify what the minimum improvement in their symptom profile would be for them to consider meaningful. Finally, participants’ understanding of the global impression of change anchor (and what influenced their response) will be explored to help understand the quantitative results.

#### Analysis

As this study uses a natural history framework for exploring change (ie, it is noninterventional), all change statistics should be considered informative but preliminary only. Reliability and measurement error statistics can be calculated in the subsample of participants whose health status “stayed the same” between stage 3 and stage 4. Specifically, the intraclass correlation coefficient will be used to assess test-retest reliability, while the standard error of measurement and minimum detectable change at the 95% confidence level will be used to estimate measurement error in “stable” participants.

Preliminary analyses of responsiveness (ie, in the absence of an intervention) will be estimated using the standardized response mean (for improved, stable, and worsened participants) and the receiver operating characteristic area under the curve for the improved subgroup.

To estimate improvement-based MIC, the mean and median change in symptom burden (between stage 3 and stage 4) among participants who reported a minimal improvement in health (ie, “improved somewhat”) will form the primary anchor-based MIC. A secondary anchor approach will compare change in symptom burden with change in PHQ-15 scores, with an “improved” group defined by (1) a PHQ-15 score greater than or equal to the estimated MIC for the PHQ-15 of 3 points [61] and/or (2) categorical improvement in PHQ-15 clinical cutoff groups (eg, from “moderate” to “mild” symptoms) [55]. These anchor methods will be supplemented with distribution-based analyses using standard approaches (ie, 0.5 × SD and standard error of measurement) [59]. Change in worsened groups will be calculated and reported for comparative purposes but is not the primary focus of interest. Finally, responder difference will be estimated using (1) the binary method, whereby the proportion of people in improved vs not improved subgroups experiencing improvement above the MIC is estimated; and (2) the mean method, whereby the difference in mean burden change for the improved vs not improved subgroups is calculated [62].

Analysis of the qualitative interviews will involve a quantitative estimate of meaningful improvement and thematic coding of supportive quotes to understand patients’ rationale for meaningful change [63]. Qualitative data will be analyzed using a hybrid inductive-deductive content analysis approach [64], commonly used in interviews with concept elicitation elements [65,66]. Reflexivity and trustworthiness will be addressed using the same methods as in stage 2. Ultimately, recommendations for a preliminary minimal clinically important difference (improvement-focused) will be informed by input from clinical and patient advisors in the MAG, triangulating clinical opinion with the available quantitative and qualitative data on meaningful change. Values will be rounded to possible scores on the instrument where relevant, and it is possible that a range (eg, with a lower and upper bound) rather than a single value may be proposed [58].

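### The secondary PHQ-15 anchor's improved group has no upper limit and an unresolved and/or, so it is not a minimally improved group and a MIC read from it tends to come out too high

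*Protocol article*

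**What the plan says.** The Stage 4 Data Collection section sets a five-level global rating of change as the primary anchor: "improved a lot, improved somewhat, stayed the same, worsened somewhat, or worsened a lot". Large and small improvement are separate answers. In the Stage 4 Analysis section the primary MIC is the mean and median ISBUS change among "participants who reported a minimal improvement in health", that is, the somewhat-improved answer only. Table 2 agrees: "Anchor-based MIC (mean and median improvement) for the minimally improved group".

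The PHQ-15 is the second anchor. Data Collection says: "as a secondary construct-specific anchor, existing estimates of MIC for PHQ-15 and/or preestablished clinical cutoffs for the measure will be used". The Analysis section opens its rule with "A secondary anchor approach will compare change in symptom burden with change in PHQ-15 scores" and then defines the improved group by two routes joined by and/or:

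- Route 1: "a PHQ-15 score greater than or equal to the estimated MIC for the PHQ-15 of 3 points".
- Route 2: "categorical improvement in PHQ-15 clinical cutoff groups", with a move from moderate to mild as the example.

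Neither route has an upper limit. The article does not say whether the routes are to be combined as a union, as an intersection, or used one at a time.

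**The concern.** An anchor-based MIC is meant to be the score change that goes with a small but noticeable improvement. The primary anchor respects this by leaving out those who improved a lot. The PHQ-15 anchor does not: a 10-point fall counts the same as a 3-point fall. The average ISBUS change in such a group reflects the average improver, not the minimal one.

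Two wording problems add to this. Route 1 tests a score of 3 or more where a reduction of 3 or more must be meant; the PHQ-15 measures symptom severity, so the literal rule would pick people who still have symptoms. And the open and/or lets the group's make-up change with the reading.

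The PHQ-15 is the only second anchor. A value that is high because of how its group is defined could pull the triangulated recommendation upward, or appear to disagree with the primary anchor for no clinical reason.

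**Working it through.** The article states no MIC value, SD or sample size for this anchor, so there is no planned figure to reproduce. The check asks how far the average PHQ-15 fall in the improved group lies from 3 points.

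**From the article:** threshold 3 points; no upper limit on either route; routes joined by and/or; 32 follow-up surveys completed by March 2026 (Results).

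**Assumed, not in the article:**
- The PHQ-15 fall *d* from stage 3 to stage 4 is normal with mean 0, rounded to whole points, with SD 2 to 6.
- PHQ-15 categories are 5 points wide and baseline position within a category is uniform, so a fall of *d* points crosses a cutoff with probability min(1, *d*/5).
- Expected ISBUS improvement is linear in the fall, *b* × *d* with *b* > 0.

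**Formulas.** P(*d*) = Φ((*d*+0.5)/SD) − Φ((*d*−0.5)/SD). The group mean fall is Σ *d*·w(*d*)·P(*d*) / Σ w(*d*)·P(*d*), with weights:
- Route 1 alone: w = 1 for *d* ≥ 3, otherwise 0.
- Or: w = 1 for *d* ≥ 3; w = *d*/5 for *d* = 1 or 2.
- And: w = min(1, *d*/5) for *d* ≥ 3, otherwise 0.
- Route 2 alone: w = min(1, *d*/5) for *d* ≥ 1.

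The ISBUS change matching a 3-point fall is 3*b*, and the group's mean ISBUS change is *b* × (mean fall). The ratio is therefore (mean fall)/3, and *b* cancels.

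| SD of change | Route 1: mean fall (ratio to 3) | Or | And | Route 2 alone |
|---|---|---|---|---|
| 2 | 3.53 (1.18) | 2.67 (0.89) | 3.68 (1.23) | 2.57 (0.86) |
| 3 | 4.22 (1.41) | 3.57 (1.19) | 4.48 (1.49) | 3.63 (1.21) |
| 4 | 4.96 (1.65) | 4.40 (1.47) | 5.28 (1.76) | 4.57 (1.52) |
| 5 | 5.72 (1.91) | 5.21 (1.74) | 6.07 (2.02) | 5.44 (1.81) |
| 6 | 6.50 (2.17) | 6.01 (2.00) | 6.86 (2.29) | 6.28 (2.09) |

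Example: at SD 4, route 1 gives 4.96/3 = 1.65.

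**Why the readings differ.** Under or, falls of only 1 or 2 points that happen to cross a cutoff enter the group and make up 44%, 25%, 17%, 13% and 10% of it for SD 2 to 6. They pull the mean down. Falls of 6 points or more, twice the threshold, make up 3%, 16%, 32%, 44% and 53% of the route 1 group and pull it up.

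**Numbers of people.** Of 32 follow-ups, route 1 would hold about 3.4 at SD 2 and 10.8 at SD 6, so a few large improvers can dominate the mean. The median is less affected.

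**Against a minimal band.** A fall of 3 to 5 points, an illustrative band, has mean 3.45, 3.72, 3.84, 3.89 and 3.93. Relative to it, route 1 is 1.02, 1.13, 1.29, 1.47 and 1.66 times as large, and the or reading 0.77, 0.96, 1.15, 1.34 and 1.53 times.

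**The case against.** The strongest reply is that upward bias is not built in. A reader who stops at route 1 might conclude that the secondary MIC must be overstated. Route 2 admits small falls across a cutoff, and with SD 2 under or, or under route 2 alone, the group mean is below 3 points. Against a 3-to-5-point band, the or reading shows no inflation at SD 3 either (0.96). This stands: the direction is likely, not certain.

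Second, the estimator is not stated for this anchor. The article says only that changes in the two scores will be compared. Table 2 names the mean and median "for the minimally improved group", which may refer to the primary anchor alone. An uncapped improved group is also what the responder-difference analysis in the same paragraph needs. This too stands, so the point is conditional on the group's average being used as a MIC.

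Third, a reader might infer from route 1 that a 3-point rise, or any remaining score of 3 or more, would count as improvement. The sentence as a whole does not support that: it opens with change, calls the group improved and gives moderate to mild as its example. This is a drafting error, not a risk to the analysis.

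Fourth, it would be wrong to call this the only quantitative check on the primary MIC. Distribution-based values and an interview-based estimate are also planned. All change statistics are labelled preliminary, and the final recommendation is triangulated and may be a range.

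None of this makes the secondary group a minimally improved one.

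**Conclusion.** The concern holds in a limited form. The secondary PHQ-15 group has no upper limit by either route, which does not fit the primary anchor or Table 2. If its mean or median ISBUS change serves as a MIC, the result tends to exceed the change matching a 3-point PHQ-15 improvement.

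For the mean, the excess is about 20% to 120% for route 1 alone. Under the or reading it runs from 11% below to 100% above. Every reading is above 3 points once the SD of PHQ-15 change reaches 3. These figures rest on assumed normal change with mean 0, a linear ISBUS/PHQ-15 relation and, for route 2, 5-point categories; none comes from the article. The size cannot be fixed until the SD is known and the and/or is settled.

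The rule should be corrected, but the consequence is modest: this is a secondary, preliminary input to a triangulated judgement.

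**What to change.** 1. Replace the route 1 wording with: a reduction in PHQ-15 score from stage 3 to stage 4 of at least 3 points.
2. Choose and or or for the two routes, and say so.
3. Take the secondary MIC as the ISBUS change predicted at a 3-point reduction, from a regression of ISBUS change on PHQ-15 change in all follow-ups. As a sensitivity analysis, report the ISBUS change in a minimal band with a lower bound of 3 and a justified upper bound.
4. Keep the uncapped improved group for the responder-difference analysis and as a descriptive result.

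The cost is a reworded sentence and one simple analysis; no new data items are needed. Stage 4 was still open at submission, so the rule could be settled before its analysis. The regression assumes linearity. A band leaves very few people: under the assumptions above, a 3-to-5-point band would hold about 3 to 6 of 32.
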